#### Secondary outcomes

Secondary outcomes are as follows:
Ovulation rate;Basal body temperature;Serum sex hormones: FSH, LH, PRL, E_2_, P, T;Serum AMH and inhibin B;Uterine and bilateral ovarian volumes at the early follicle phase;Thickness and type of endometrium at the early follicle phase;Antral follicle count and the size of dominant follicle;Peak-systolic flow velocity, pulsatility index, and resistance index of the uterus and bilateral ovaries;Serum coagulation indicators;Traditional Chinese medicine symptom score.

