Current clinical trials have shown that traditional Chinese medicine (TCM) was associated with significantly higher pregnancy rates than control treatments, and the ovulation rates between the two groups were not significantly different [9–11]. It is notable that all systemic reviews and meta-analyses have mentioned that there is a lack of high-quality, strong, evidence-based, large-sample randomized controlled trials (RCTs) on this topic.

Bushen Culuan Decoction was created more than 20 years ago. In a previous experimental study evaluating the effectiveness and safety of Bushen Culuan Decoction in treating anovulatory infertility, it was found that Bushen Culuan Decoction had no adverse effect or toxic reaction in acute toxicity tests, reproductive toxicity tests, genetic tests, and teratogenic toxicity tests [12] and significantly promoted follicle maturation, ovulation, and luteinization [13]. A clinical exploratory study showed that Bushen Culuan Decoction significantly increased the pregnancy rate, depressed serum prolactin (PRL), and elevated serum estradiol (E_2_) compared with the control treatment in women with anovulatory infertility [14].

Until now, most studies about TCM treating anovulatory infertility have focused on a single disease in a single center, and there is no study with a large sample size aiming to verify the effectiveness and safety of Bushen Culuan Decoction in treating anovulatory infertility. Based on the results of previous studies, we hypothesized that Bushen Culuan Decoction would improve the pregnancy rate by promoting follicle development and ovulation and improving endometrial receptivity. This study will evaluate that hypothesis.

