### Effectiveness index

The effectiveness index is divided into 6 parts.
The date and duration of LMP and BBT analysis. BBT will be analyzed by the clinical investigator, and the result will be categorized as single-phase, double-phase, or atypical double-phase, along with the duration of the high-temperature phase.Sex hormone. Sex hormones, including FSH, LH, PRL, E2, P, and T, will be taken one or two times before the baseline visit and will be recorded at the baseline visit. The first blood sample collection will be in the follicular phase of the menstrual period, which is days 3–5 of the menstrual period. The second blood sample collection will be at the ovulatory phase, as confirmed by a positive ovulation test result. If the participant does not have a typical menstrual period or cannot identify the ovulatory phase, she will take the blood sample once and record the date of LMP.Serum INHB and AMH. These two indicators will not significantly change within a menstrual period, so we will take them at the same time as the first collection of sex hormones.Coagulation indicators. Blood samples will be collected at the same time as the first collection of sex hormones in order to measure coagulation indicators, including PT, TT, APTT, and FIB.Transvaginal ultrasound. The first transvaginal ultrasound will be done 3–5 days after the menstrual bleeding has ended. The information collected at this time will be uterine and bilateral ovarian volumes, the thickness and type of endometrium, bilateral ovarian antral follicle count, uterine and bilateral ovarian peak-systolic flow velocity, pulsatility index, and resistance index. On the 12th day of the menstrual period, the participant will start to monitor the ovulation every day, and the size of the dominant follicle will be recorded.Traditional Chinese medicine symptom score. The clinical investigator will show the participant the form and explain every detail to ensure that the participant fully understands it and let her choose every answer. The form is shown in Table 2.

**Table 2 Tab2:** Traditional Chinese Medicine symptom score

Kidney deficiency pattern	Traditional Chinese Medicine symptom score standard (point)			
	0	1	2	3
	Never happened	Mild symptom or happened occasionally	Medium symptoms or happened sometimes	Severe symptoms or happened frequently
Amenorrhea				
Delayed menstruation				
Scant menstruation				
Weakness in lower back, waist and knees				
Dizziness and tinnitus				
sexual apathy				

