### Treatment visit

After getting the medication package, every participant will start medical treatment on day 5 of the 1st menstrual period and visit the clinical investigator on day 25 of the 1st menstrual period or on day 1 of the 2nd menstrual period if the menstrual period duration is less than 25 days. In every treatment visit, relevant information about the participant will be recorded, and she will be given the medication package for the next menstrual treatment period.

In the 1st and 2nd menstrual periods, the participant will start to monitor ovulation every day from the 12th day of menstruation, and the size of the dominant follicle will be recorded. If there is ovulation, a urine pregnancy test will be performed to exclude pregnancy. If there is no pregnancy, the treatment will be continued in the next period. The detailed medication use status, the date and duration of the last menstruation period along with BBT, and ovulation monitoring results will be recorded, and the traditional Chinese medicine symptom score will be evaluated.

In the 3rd menstrual period, serum sex hormones at the ovulatory phase will be tested and recorded in addition to all information collected in the previous period. If there is no ovulation, the blood sample for sex hormone testing will be collected on the 15th day of the menstrual period.

After treatment for 3 periods, we will analyze the ovulation of every participant. The participant will be considered to have regained regular ovulation successfully if she had ovulation in all of the past 3 periods. The treatment of the participant will be terminated, and she will have an end-of-treatment visit and then move forward into the follow-up stage. If the participant ovulates fewer than 3 times, she will go into the second treatment cycle.

For every participant in the second treatment cycle, she will have a 4th, 5th, and 6th treatment visit. The procedures of the 4th and 5th treatment visits will be the same as those of the 1st and 2nd visits, and the 6th visit will be the same as that of the 3rd visit. After the 6th menstrual period treatment, all participants will stop treatment and move into the next stage regardless of whether they recover regular ovulation.

If the participant gets pregnant in the treatment process, she will stop the treatment immediately and move into the end-of-treatment visit and follow-up stage.

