#### Statistical analysis

An independent statistician will use SPSS 21.0 (SPSS, Chicago, Illinois, USA) to analyze the data.

The mean ± SD will be used to describe normally distributed data, while medians with IQRs will be used if the data are not normally distributed. The *χ*^2^ test will be used for evaluating differences between dichotomous variables, while one-way analysis of variance or Student’s *t* test will be used for evaluating continuous variables. The Mann-Whitney test will be used if the data are not normally distributed. A *p* value < 0.05 will be considered statistically significant.

If there are dropouts from the study, the last-observation-carried-forward principle will be used to compensate for the loss of data.

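### The secondary outcome of dominant-follicle size has no value in a period without a dominant follicle, so as written it compares the arms only where a response occurred and cannot by itself test follicle development

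*Protocol article*

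**What the plan says.** The Background gives the hypothesis: the decoction will "improve the pregnancy rate by promoting follicle development and ovulation and improving endometrial receptivity". Follicle development is therefore one of the claimed mechanisms.

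The outcome offered for it, under Secondary outcomes, is "Antral follicle count and the size of dominant follicle". For the baseline visit, the Effectiveness index section says that from day 12 "the participant will start to monitor the ovulation every day, and the size of the dominant follicle will be recorded". For the 1st and 2nd menstrual periods, the Treatment visit section says "the participant will start to monitor ovulation every day from the 12th day of menstruation, and the size of the dominant follicle will be recorded", and later periods follow the same procedures. No section defines dominance or says what is entered when no follicle becomes dominant.

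The Treatment visit section does foresee failure to ovulate and gives a substitute sampling day for hormones: "If there is no ovulation, the blood sample for sex hormone testing will be collected on the 15th day of the menstrual period". It gives no equivalent for follicle size.

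Under Statistical analysis, one-way analysis of variance or Student's t test "will be used for evaluating continuous variables", and "The Mann-Whitney test will be used if the data are not normally distributed". The only missing-data rule there is last observation carried forward for dropouts.

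**The concern.** A t test or Mann-Whitney test uses only women who have a number. A woman who attends every scan and grows no dominant follicle has none. She has not dropped out, so the carry-forward rule does not reach her. Whether she has a number depends on whether treatment worked, so the women compared are selected after randomisation, possibly differently in the two arms.

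Two things follow for this outcome. An arm in which fewer women grow a follicle is not marked down for it. An arm that brings in additional, marginal responders may have its mean pulled down by them. The comparison could then show nothing, or point the wrong way, while follicle development was in fact promoted.

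**Working it through.** **Is there a value for the empty case elsewhere in the article?** The notes to Table 1 mention sizes of developing follicles, which would not require dominance. They belong to the general transvaginal ultrasound row, ticked only at baseline and end of treatment, and the End-of-treatment visit section skips that scan in pregnant women. The row ticked in every treated period is ovulation monitoring, for which the text records the dominant follicle only. The developing-follicle sizes are not a named outcome. They do not fill the gap.

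**The plan's own figures.** The article gives no expected follicle size, standard deviation or response rate, so there is no follicle figure to reproduce. I take only the arm size from Sample size estimation, 219 per group. It reproduces with the stated rates of 90% and 80%, power 90% and one-sided α 0.05: (1.645 + 1.282)² × 2 × 0.85 × 0.15 / 0.10² = 218.4, rounded up to 219. This has no bearing on the follicle outcome.

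**Illustration; every follicle input is assumed.**
- Control arm: 60% grow a dominant follicle, mean 20 mm, SD 3.
- Better arm: 80% do. The same 60% are unchanged, and the extra 20% average m mm, SD 3.
- Women without a dominant follicle: largest follicle 8 mm.
- One value per woman.

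Responders-only mean in the better arm = (0.60 × 20 + 0.20 × m) / 0.80; control = 20.

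All-women mean in the better arm = 0.80 × (responders' mean) + 0.20 × 8; control = 0.60 × 20 + 0.40 × 8 = 15.2.

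Worked at m = 16:
- Responders' mean: (12 + 3.2) / 0.80 = 19.0, a difference of −1.0 mm.
- Variance in the better arm: 9 + 0.75 × 1² + 0.25 × 3² = 12.
- Responders: 219 × 0.80 = 175.2 and 219 × 0.60 = 131.4.
- SE = √(12/175.2 + 9/131.4) = 0.370, so z = −2.7.
- All women: 0.80 × 19.0 + 1.6 = 16.8, a difference of +1.6 mm.

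| Mean of extra responders (mm) | Responders-only difference (mm) | z | All-women difference (mm) |
|---|---|---|---|
| 20 | 0.0 | 0.0 | +2.4 |
| 18 | −0.5 | −1.4 | +2.0 |
| 16 | −1.0 | −2.7 | +1.6 |
| 14 | −1.5 | −3.8 | +1.2 |

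With 70% responding in the better arm, the responders-only difference runs from 0 to −0.9 mm and the all-women difference from +1.2 down to +0.6 mm. With 90%, the ranges are 0 to −2.0 mm and +3.6 down to +1.8 mm.

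**The yes/no outcome in the same example.** It compares 80% with 60% over all 219 per arm, whatever m is. SE = √(2 × 0.70 × 0.30 / 219) = 0.0438, so z = 0.20 / 0.0438 = 4.6.

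**The case against.** The strongest objection is that the article nowhere says the analysis is restricted to responders. Dominance is undefined, and site staff might record the leading follicle in every woman, which is close to what is asked for here. The case report form or an analysis plan that is not shown could settle the coding. This stands in part: the restriction is inferred from the named variable, the tests and the dropout-only rule. But the choice of variable is made in this document. If only dominant follicles are sized, no later analysis can recover the leading follicle in the other women.

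A reader might also infer that treatment failures disappear from the trial's evidence. They do not. Pregnancy is the primary outcome, ovulation rate is the first secondary outcome, and both can count every woman. An arm with fewer responders is penalised on both.

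A reader might infer that a wrong-direction result is likely. The documents do not support that. A reversal needs extra responders with clearly smaller follicles: at 18 mm in the 80% versus 60% example it is −0.5 mm with z only −1.4. Each woman is also monitored over three to six periods, so fewer women would lack any value at all than the example assumes.

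Nor does the text show that most participants will lack a dominant follicle. LUFS is diagnosed in women whose follicle grows and does not rupture, and corpus luteum insufficiency is defined by the luteal phase. The problem will differ across the six diseases.

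Finally, replacing the outcome with largest diameter in everyone, read as benefit, would misfire. The LUFS criteria describe a retained follicle of 25 mm in one subtype and one of 31–50 mm in another, so persistent disease could score best. This objection stands and shapes the fix.

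**Conclusion.** The point holds in limited form. Taken as written, dominant-follicle size is compared only where a dominant follicle arose, so it is not a randomised comparison of all women and cannot by itself carry the follicle-development hypothesis. It may show no difference, or a reversed one if additional responders have smaller follicles. The direction of the distortion follows from the definition; its amount rests wholly on assumed rates and sizes and is no forecast for this trial. Because it concerns half of one item in a list of ten secondary outcomes, and pregnancy and ovulation rate are untouched, the severity is minor to moderate.

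**What to change.** In Secondary outcomes, Effectiveness index and Treatment visit:

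1. Add the outcome dominant follicle developed (yes/no), by a size set in advance, with all randomised women as denominator. Let it lead. Assess it over a window all women share, such as the first three menstrual periods, because only women who did not ovulate in all three enter the second treatment cycle.
2. Record the leading follicle diameter for every woman scanned in each monitored period, whether or not it becomes dominant.
3. Report dominant-follicle size among women who have one as descriptive only, with no test between arms.
4. Do not read a larger diameter as benefit in LUFS. Report follicle size by disease, or leave LUFS out of the diameter comparison.

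The cost is small: changes to the case report form and wording, since daily monitoring from day 12 is already planned. The diameter over all women will probably have two humps, which is a further reason for the yes/no outcome to lead. Any period already recorded with the dominant follicle only cannot be completed later unless the scan records hold the other sizes.

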### Safety analysis

Safety will be analyzed by adverse events (AEs); laboratory tests, including routine blood and urine tests, liver and renal function tests; and ECG. AEs will be recorded at every visit, and the other tests will be done at the baseline visit and end-of-treatment visit. Every AE will be recorded in detail, including the starting time and ending time, severity, characteristics (continuous or paroxysmal, and the frequency), any relationship with the drugs used in the study, the outcome, use or nonuse of corrective treatment, and whether the woman drops out of the study because of the AE. In this study, common AEs will include nausea, loose stool with dark color, and mild pain in the lateral lower abdomen on ovulation day, which are not expected to be severe and have no need of intervention. If the participant has serious adverse events (SAEs) leading to extended hospitalization, death, or a status that the PI considers unsuitable for further study, she will be removed from the trial as soon as possible and provided proper treatment. Every SAE will be recorded in the CRF and reported to the ethics committee and related health administrative department.

The degrees of safety analysis are divided into 4 grades according to the AE and the safety index profile:
Grade 1: The participant is safe without any AE. There is no abnormal result in the safety index.Grade 2: The participant is relatively safe with a mild AE. The adverse reaction has no need of treatment, and the participant can continue the study. There is no abnormal result in the safety index.Grade 3: There is moderate AE, or there is a mildly abnormal result in safety index. The participant can continue the study after corrective intervention for the AE.Grade 4: The participant should be removed due to the SAE, or there is a moderate or serious abnormal result in safety index.

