**Methods:**

This is a randomized, double-blinded, double-dummy, parallel, positively controlled, adaptive, multicenter clinical trial. All participants will be randomly allocated by a central randomization system to the treatment group or the control group in a 1:1 ratio. The treatment group will undergo a 14-day treatment with Bushen Culuan Decoction 13 g three times a day and a 5-day treatment with clomiphene citrate placebo tablets 50 mg once a day starting on day 5 of every menstrual period. The control group will undergo a 14-day treatment with Bushen Culuan Decoction placebo 13 g three times a day and a 5-day treatment with clomiphene citrate tablets 50 mg once a day from day 5 in every menstrual period. The whole treatment will last through 3 menstrual periods or 6 menstrual periods, depending on whether ovulation is regained in the first 3 menstrual periods. All statistical analyses will be performed in SPSS 21.0 (SPSS, Chicago, Illinois, USA), and a *p* value < 0.05 will be considered statistically significant.

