### Interventions

Eligible patients will be randomly allocated into one of the two arms. Experimental group: Bushen Culuan Decoction, containing the ingredients of Ligustrum lucidum, dodder, Xianling spleen, Morinda officinalis, Eupatorium adenophorum, Salvia miltiorrhiza, Angelica sinensis, Ligusticum chuanxiong, red peony, raw dandelion (made by Beijing Tcmages Pharmaceutical Co, Beijing) with clomiphene citrate placebo tablets (made by the drug manufacturing department of Xiyuan Hospital). Both drugs will be started on day 5 after a spontaneous menstrual period or after vaginal withdrawal bleeding following progesterone (100 mg twice a day for 6 days, Zhejiang Xianju Pharmaceutical Co, Taizhou) if the participant does not have a regular menstrual period. Bushen Culuan Decoction will be taken at 13 g three times a day for 14 days, while clomiphene citrate placebo tablets will be taken at 50 mg once a day for 5 days. Each treatment cycle will contain 3 menstrual periods. If the participant regains regular ovulation at the end of the first, her treatment will end, and if not, she will start the second treatment cycle. All treatments will be terminated after 2 treatment cycles. If the participant is pregnant, all treatment will be stopped, and she will be moved into the follow-up stage.

Control group: clomiphene citrate tablets with Bushen Culuan Decoction placebo treatment (made by Beijing Tcmages Pharmaceutical Co, Beijing). Clomiphene citrate tablets (Fertilan®, Codal Synto Ltd. Cyprus) will be taken at 50 mg once a day for 5 days, while Bushen Culuan Decoction placebo will be taken at 13 g three times a day for 14 days. The starting time, termination time, and treatment cycle will be the same as those of the experimental group.

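### The per-woman safety grade takes no account of treated time, which depends on ovulation and pregnancy, so it can differ between arms at equal AE risk per treated period

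*Protocol article*

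**What the plan says.** All references are to the protocol article.

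- **Treatment length.** The abstract's Methods paragraph states: "The whole treatment will last through 3 menstrual periods or 6 menstrual periods, depending on whether ovulation is regained in the first 3 menstrual periods". The Treatment visit section gives the rule: "The participant will be considered to have regained regular ovulation successfully if she had ovulation in all of the past 3 periods". For such a woman, "The treatment of the participant will be terminated, and she will have an end-of-treatment visit". Otherwise: "If the participant ovulates fewer than 3 times, she will go into the second treatment cycle".
- **Pregnancy.** Under Interventions: "If the participant is pregnant, all treatment will be stopped, and she will be moved into the follow-up stage".
- **AE collection.** Under Safety analysis: "AEs will be recorded at every visit". Start and end times are among the details recorded for each AE.
- **Laboratory tests and ECG.** In the same section: "the other tests will be done at the baseline visit and end-of-treatment visit".
- **Safety summary.** Each participant receives one of four grades, built from AEs and the safety index together. The top grade reads "Grade 1: The participant is safe without any AE", and it also requires a normal safety index.
- **Tests.** Statistical analysis names the chi-square test, analysis of variance, the t test and the Mann-Whitney test, without saying which applies to safety.
- **Table 1.** The row for AEs and concomitant medications has no tick in the follow-up column.

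**The concern.** The time during which a woman takes study drug and attends treatment visits is set after randomisation by how well treatment works. A woman who ovulates in all of periods 1–3 has three treated periods in which an AE can arise; one who does not has up to six; one who conceives has fewer than she would otherwise have had. A grade that asks whether she ever had an AE grows with that time and does not record it.

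The Background hypothesises that the decoction acts partly by promoting ovulation, and it is meant to raise pregnancy. If it does either more than clomiphene, its arm is treated for less time and would usually look safer at equal toxicity; if it does less, it would usually look more harmful. In both cases a between-arm difference in grade mixes efficacy with toxicity. The laboratory and ECG part of the grade has the same difficulty, because those tests follow whichever treatment length applied.

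**Working it through.** **Plan's own figure.** None exists to reproduce. The document gives no AE frequency, ovulation rate by arm or expected exposure. The 219 per group in Sample size estimation is used below only as an arm size.

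**Assumptions (not in the documents).** AE risk *h* per treated period is the same in both arms, constant, and independent between periods. The share stopping after period 3 is *s*.

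**Step 1: risk of any AE by treatment length.**
- Three periods: 1 − (1 − *h*)³. At *h* = 0.05: 1 − 0.8574 = 14.3%.
- Six periods: 1 − (1 − *h*)⁶. At *h* = 0.05: 1 − 0.7351 = 26.5%.

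**Step 2: arm-level risk.** P(any AE) = *s* × (three-period risk) + (1 − *s*) × (six-period risk).
- *s* = 0.60: 0.60 × 0.1426 + 0.40 × 0.2649 = 19.2%.
- *s* = 0.30: 0.30 × 0.1426 + 0.70 × 0.2649 = 22.8%.
- The gap is 3.7 points with no difference in risk per period. With 219 per arm, a two-sided 5% test would call it significant about 16% of the time.
- For *h* from 3% to 10%, and stopping at 50% vs 25% or 60% vs 30%, the gap runs from 2.0 to 5.9 points.

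**Step 3: the same through the ovulation rule.** If ovulation has probability *q* per period, a woman stops after period 3 with probability *q*³. At *h* = 0.05, without pregnancies:

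| *q* per period | Extended (1 − *q*³) | Mean treated periods | Any AE |
|---|---|---|---|
| 0.9 | 27% | 3.81 | 17.6% |
| 0.8 | 49% | 4.46 | 20.2% |
| 0.7 | 66% | 4.97 | 22.3% |
| 0.6 | 78% | 5.35 | 23.8% |

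Two arms with the same *q* have the same risk. Between 0.8 and 0.6 the ratio is 1.18; between 0.9 and 0.6 it is 1.36.

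**Step 4: pregnancy alone.** Take *q* = 0.8 in both arms, *h* = 0.05, and conception in 15% vs 5% of ovulatory periods. Mean treated periods are 3.63 vs 4.17 and any AE is 16.7% vs 19.0%. Equal ovulation therefore does not by itself equalise exposure.

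**Step 5: cases that run the other way.**
- Ovulation-day pain is listed under Safety analysis as a common AE. If it adds 10% per ovulatory period to a 2% base risk, *q* = 0.8 vs 0.6 gives 36.9% vs 35.7%: the higher-ovulating arm now looks worse.
- If the lower-ovulating arm conceives more often (*q* = 0.7 with 15% conception, against *q* = 0.8 with 5%), any AE at *h* = 0.05 is 18.5% vs 19.0%, again reversed.

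**Step 6: does the remedy remove it?** Without ovulation-linked AEs, AEs divided by treated periods return *h* in both arms, a ratio of 1.00. Any AE in periods 1–3 is 14.3% in both arms if nobody conceives. With conceptions a small gap stays: at *q* = 0.8 with 15% and *q* = 0.6 with 10% it is 12.7% vs 13.5%, against 16.7% vs 21.2% over all treatment.

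**The case against.** **The direction is not certain.** A reader might infer that the arm that ovulates less must show more AEs. The documents do not support that. Ovulation-day pain accrues with ovulation, conception also cuts exposure, and Step 5 shows either can reverse the sign. This stands, and the point is limited accordingly.

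**The grade may not be the between-arm test.** The section says safety is analysed through AEs, laboratory tests and ECG. It does not say that the grade is the tested endpoint or that the worst grade counts, and exposure-adjusted rates are often left to an analysis plan. That is fair as to what is missing. What remains is what the article fixes: a participant-level scale whose best level requires no AE at all, over a duration set by response. An analysis plan that applies it as written inherits the problem.

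**Any AE over the whole regimen is a legitimate quantity.** Women on a regimen that needs six periods more often do face that risk. This stands. A reader might go further and conclude that the graded comparison says nothing about safety, but that is too strong: it describes the strategy as delivered and does not separate toxicity from duration.

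**The size is assumed.** No AE or stopping rate is given, and the Background cites earlier trials of traditional Chinese medicine without a significant ovulation difference. The gap is nil if ovulation and pregnancy are both equal, and it shrinks if AEs recur in the same women. But the same sentence reports higher pregnancy rates, and pregnancy shortens exposure too (Step 4).

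**Table 1 is weak evidence.** Its pregnancy and neonatal row has no ticks at all, although Follow-up visit requires those data, so a blank cell proves little. The AE row is an inconsistency to reconcile and carries no weight in the exposure argument.

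**Conclusion.** The point holds in a conditional form. The safety grade is per woman, treated and AE-observed time depends on ovulation and pregnancy, and the grade makes no allowance for it. If the arms differ on either outcome, the grade is expected to differ even at equal AE risk per treated period, usually to the disadvantage of the arm treated longer. On the assumed stopping shares in Step 2 the gap is about 2 to 6 points in the proportion with any AE; in the ovulation scenarios of Step 3 it can reach a ratio of about 1.4. These figures rest on constant, independent and equal AE risk per period and on assumed ovulation or stopping rates, none of which the documents supply. The premises about duration, pregnancy and the grade need no assumption. The bias is modest, but the remedy is cheap enough that it should be adopted.

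**What to change.** 1. For the between-arm AE comparison, add AE rates per treated woman-period over all treatment, by arm.
2. Add the proportion of women with any AE in periods 1–3, by arm. Restrict this to AEs: the full grade cannot be formed at period 3, because women who continue have no safety laboratory tests or ECG then.
3. Report the number of treated periods by arm, and show ovulation-day pain separately, since a per-period rate does not remove its link to ovulation.
4. Keep the four-level grade over all treatment as a descriptive summary, tabulated by number of treated periods, and read laboratory and ECG findings against that number too.
5. Separately, reconcile the AE row of Table 1, which has no follow-up tick, with the statements under Study-specific visits and procedures and Safety analysis that AEs are recorded at each visit.

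The cost is a little more analysis work and some wording. AE start and end times are already collected, and nothing changes in treatment, visits or sample size. One limit remains: early conceptions leave exposure slightly unequal within periods 1–3, so items 1 and 2 should be read together.
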